### Protocol amendments

2.11

Any amendments to the protocol and information provided to participants will be submitted to the REC for approval before implementation. Substantial amendments may only be implemented after REC approval has been obtained, whereas nonsubstantial amendments can be implemented without written approval from the REC. Data and source documents will be stored such that they can be accessed at a later date for monitoring or inspection by the REC. After the end of the study, the results will be submitted for publication in a peer-reviewed journal, following CONSORT and SQUIRE compliance guidelines. Authorship of any related presentations or reports will be under the name of the collaborative group.

## Discussion

3

Transcutaneous PTNS has a well-established role in the treatment of children with urinary dysfunction and adults with fecal incontinence.^[20,21,25]^ There is evidence that PTNS can stimulate both the second and third sacral nerve roots, which are the same spinal segments that innervate the bladder, rectum and pelvic floor, thus modulating bowel motility and assisting in the treatment of constipation.^[26,36,37]^ On the other hand, although transcutaneous PTNS can be considered an auspicious, noninvasive and safe method to be used in the pediatric age group, there is still no published study that has investigated its use in children for the treatment of constipation.

The main objective of this study is to assess the applicability and clinical outcomes of transcutaneous PTNS in children with FC. It is intended to demonstrate the efficacy of this promising method to increase the number of complete spontaneous bowel movements, the consistency of stool, to reduce the number of episodes of retentive fecal incontinence, and improve the overall quality of life. This study is currently in the recruitment phase, which began in April 2019.

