In 2014, the European Society for Pediatric Gastroenterology, Hepatology, and Nutrition and the North American Society for Pediatric Gastroenterology, Hepatology, and Nutrition published a guideline that provides evidence-based recommendations for the evaluation, treatment, and follow-up of children with FC.^[3]^ The well-founded point for the treatment of FC consists of education of the child and parents, behavioral modifications, and laxative therapy.^[3,12]^ Therefore, conventional medical management of FC consists of pharmacological and nonpharmacological interventions. The pharmacological treatment of FC with laxatives involves 3 steps; disimpaction, maintenance treatment, and weaning. Nonpharmacological interventions involve education, demystification, explanation, guidance for toilet training, scheduled toilet sits, establishing a reward system, and keeping a defecation diary.^[3,13,14]^

In tertiary care centers, approximately 50% of children with FC managed with conventional treatment will be recover and taken off laxatives within 6 to 12 months, but the others, the symptoms can persist into adulthood despite intensive laxative treatment.^[15]^ Thus, a subset of patients may present with an unsatisfactory response and only minor improvement of symptoms. These children experience severe and long-lasting symptoms with recurrent fecal impactions, clinically characterized by extended intervals between defecation episodes, the passage of a large amount of stools once every 7 to 30 days and fecal incontinence that respond poorly to conventional therapy. Accordingly, when symptoms are irresponsive to optimal conventional treatment for at least 3 months, these children are considered to have intractable FC.^[3,16]^

Unfortunately, treatment options for children with constipation refractory to conventional treatment are limited. The most recent guidelines from the European and North American Pediatric Gastroenterology societies on the evaluation and treatment of FC in children recommend consideration of anal sphincter botulinum toxin injection, transanal irrigation, antegrade continence enemas, sacral nerve stimulation, and partial or total colonic resection for treatment of intractable constipation.^[3,10,17]^

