### Study design and setting

2.1

This is a single-center, interventional, prospective, and longitudinal study design to assess the applicability and clinical outcomes of transcutaneous PTNS in children with FC. This study will be conducted at the Botucatu Medical School, São Paulo State University (UNESP), São Paulo, Brazil. The data collection period will be 12 months long, and started in April 2019.

Children will be submitted to daily sessions of transcutaneous PTNS for a period of 4 weeks. All children will also be invited to participate in semi-structured interviews, 1 in each of the 3 assessments: 1 week before the start of the intervention; immediately after the 4 weeks of intervention; and 4 weeks after the end of the intervention period. In these interviews, the aspects related to bowel habits and quality of life will be assessed.

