### Patient selection and recruitment

2.3

The estimated sample size is 28 patients, calculated for a paired *t* test (before and after intervention), based on an estimated mean increase of 7 defecations per month (according to data from previous PTNS studies^[25,26]^), an estimated standard deviation of changes = 12, a 2-tailed *α* = 0.05 and a test power *β* = 0.85. The sample will be comprised of children selected from the Pediatric Gastroenterology Outpatient and Pediatric Surgery Outpatient of the Clinics Hospital of the Botucatu Medical School -UNESP. The patients will be invited to attend an initial consultation to inform them about the study methods and apply the eligibility criteria.

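### The protocol says it will demonstrate efficacy, but a single-arm before/after comparison cannot attribute a change in stool frequency to the stimulation

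*Protocol article*

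**What the plan says.** Section 2.1 describes the design: "This is a single-center, interventional, prospective, and longitudinal study design". It gives all participants the same treatment: "Children will be submitted to daily sessions of transcutaneous PTNS for a period of 4 weeks". No comparator, sham or random allocation appears anywhere in the article.

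Section 2.3 sizes the study on the within-patient change: "The estimated sample size is 28 patients", "based on an estimated mean increase of 7 defecations per month", with a standard deviation of changes of 12, two-sided alpha 0.05 and power 0.85. The tests in section 2.10 (paired t, analysis of variance, Wilcoxon, Friedman, McNemar) compare assessment time points.

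There is one assessment before treatment, one at the end of the 4 weeks and one 4 weeks later (section 2.7). A 7-day diary precedes each (section 2.8). Previously prescribed treatment continues, and the study will not prevent or postpone changes to it (section 2.5).

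The Discussion then gives two aims in consecutive sentences. The first is modest: "The main objective of this study is to assess the applicability and clinical outcomes of transcutaneous PTNS in children with FC". The second is not: "It is intended to demonstrate the efficacy of this promising method to increase the number of complete spontaneous bowel movements". The article states no limitation about the missing control.

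**The concern.** The second aim claims something the design cannot deliver. A before/after difference contains any effect of stimulation plus everything else that changes over the same weeks. The protocol itself describes several such sources:

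- ongoing conventional care, and permitted changes to it;
- extra contact through training and fortnightly supervised sessions;
- reporting by children and guardians who know that treatment is being given;
- natural improvement. The Introduction says of tertiary care that "approximately 50% of children with FC managed with conventional treatment will be recover and taken off laxatives within 6 to 12 months".

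The Introduction also cites a systematic review of transcutaneous stimulation in childhood constipation that reached no firm conclusion on efficacy and called for randomised trials.

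At stake is the headline conclusion. Read against the efficacy sentence, a significant paired test would be reported as proof that stimulation works. No later analysis plan can repair this, because the comparison group does not exist.

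**Working it through.** **Inputs (section 2.3):** n = 28; planned mean change 7 per month; standard deviation (SD) of change 12; two-sided alpha 0.05; power 0.85 (printed as beta, but it works only as power).

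**1. Reproduce the plan's figure.** The normal approximation is n = [SD × (z0.975 + z0.85) / change]² = [12 × (1.960 + 1.036) / 7]² = 26.4, so 27. Adding the small-sample term z0.975²/2 = 1.92 gives 28.3. The exact noncentral t calculation gives 84.5% power at n = 28 and 85.8% at n = 29. The stated 28 reproduces within rounding, so the arithmetic is not at fault.

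**2. What the test examines.** Write the mean change as S + B, where S is the effect of stimulation and B is the mean change that would have occurred without it. The null hypothesis is S + B = 0. One group measured over time estimates only the sum. A true change of 7 is equally compatible with S = 7, B = 0 and with S = 2, B = 5.

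**3. The change that reaches significance.** The standard error is 12/√28 = 2.268. The critical t value on 27 degrees of freedom is 2.052. The threshold is 2.052 × 2.268 = 4.65 defecations per month, whatever the split between S and B.

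**4. Chance of a significant result if S = 0.** The noncentrality parameter is B/2.268. The values of B are assumptions, because the documents give none.

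| Assumed B (per month) | B/2.268 | Probability of p < 0.05 (two-sided) |
|---|---|---|
| 0 | 0 | 5% |
| 2 | 0.88 | 14% |
| 3 | 1.32 | 25% |
| 4 | 1.76 | 40% |
| 5 | 2.20 | 57% |
| 7 | 3.09 | 85% |

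The last row is the plan's own power (84.5%) with the cause exchanged. A non-specific rise of 7 is detected as readily as a stimulation effect of 7.

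**The case against.** **The stated objective is modest.** The end of the Introduction, section 2.1 and the Discussion all speak of assessing applicability and clinical outcomes; efficacy is an aim in one Discussion sentence. This is true, and it is why rewording is enough. But that sentence directly follows the main objective and says what the study is meant to show, so the two must be reconciled.

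**The design has internal checks.** The assessment 4 weeks after treatment could show loss of effect. Laxative doses are recorded, and dose, clinical and dietary changes are analysed (sections 2.8 and 2.9). These help interpretation but do not replace a control. Persisting improvement could be carry-over or natural recovery, and a decline could follow the end of stimulation or the end of extra contact.

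**Stronger readings that the documents do not support.**

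- A reader might infer that any non-specific change, however small, produces a significant result. It does not: the observed mean must reach about 4.65 per month, and a true non-specific rise of 2 gets there only about 14% of the time.
- A reader might infer that regression to the mean explains a calculable, large share of the planned 7. The content of the eligibility table is not available here. Eligibility is applied at an initial consultation, whereas the baseline diary is a separate measurement. If the selection measure, baseline and follow-up were equally correlated, selection on the first would produce no expected shift from baseline to follow-up. Some shift is possible; its size cannot be derived.
- A reader might infer that half of these children would recover during the study anyway. The 50% figure covers 6 to 12 months. Here the first comparison spans about 5 weeks (1 + 4) and the last about 9 (1 + 4 + 4). The Introduction also stresses children refractory to treatment, who may improve less.

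**Conclusion.** The concern holds as a conflict between one stated aim and the design. The study can estimate how stool frequency and the other outcomes change within children during and after treatment. It cannot show that stimulation caused the change.

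The threshold of 4.65 per month rests only on the plan's n and SD, with the observed SD equal to the planned 12. The 14% to 85% range also rests on assumed non-specific rises of 2 to 7 per month. The conclusion does not depend on which value is right: no single-arm analysis can separate the two components.

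The finding does not mean that the sample size is wrong, or that the study is not worth doing for the objective it states elsewhere.

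**What to change.** Replace the efficacy sentence in the Discussion with wording such as:

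*The study will assess the applicability and tolerability of transcutaneous PTNS and estimate the within-patient change in bowel habits and quality of life (mean with 95% confidence interval), to inform a controlled trial. Without a control group, change cannot be attributed to stimulation, and no efficacy claim will be made.*

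Carry the same limit into the results report. Sample size and tests can stay as they are. The cost is one rewording, handled under the amendment procedure in section 2.11 if needed, and a more modest claim.

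Keeping the efficacy aim would require a different study. Assuming an SD of change of 12 in each arm, a between-arm difference of 7 per month at the same alpha and power needs 2 × 26.4 = 52.8, so 53 per arm and 106 in total. Splitting the planned 28 into 14 and 14 would give about 32% to 34% power.

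A second pre-treatment diary week is at most an optional check for drift. It is usable only in children who have not yet started, and only if no stimulation occurs in that week; training includes supervised application and may fall there. If the SD of change between the two weeks were also 12, the 95% interval with all 28 children would be about ±4.65 per month, and wider with fewer. It could not detect a placebo response to treatment.
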